**Aims and hypotheses**
Aim 1: the first aim is to evaluate the implementation effectiveness of digital peer support training between emerging adults providing support (befrienders) and emerging adults seeking help (seekers).Research question 1a: is Acceset digital peer support training an effective training curriculum in providing peer support?Hypothesis 1a: the digital peer support training is effective for befrienders in providing peer support, as demonstrated by the adoption of and fidelity to the training curriculum.Research question 1b: is the Acceset text-based intervention (ie, the platform) feasible and acceptable (ie, safe and timely) as an ongoing mechanism of support for seekers and befrienders?Hypothesis 1b: digital peer support is feasible and acceptable in offering support for emerging adults’ mental well-being, which is evidenced by 2 indicators:The engagement of the seeker-befriender-moderator interaction across the 4 time points—baseline (before the intervention), 3 weeks (conclusion of the intervention), and 6 and 9 weeks (carryover effect assessment)—that is indexed by the waiting period for seekers to receive a response. Delays are defined as a >48-hour waiting period and will be categorized based on the following reasons: (1) technical factors (eg, the befriender is not able to log into the platform to respond in time) and (2) human factors (eg, the befriender drops out from the study, and no replacement is found in time). An acceptable response time is within 48 hours, and this is emphasized during Acceset digital peer support training for befrienders [37].The use of technical features of the Acceset platform that is measured by the seeker dropout rate at each stage of engagement with the Acceset platform, the number of visits on the study registration website, the number of participants who registered with Acceset, the average number of letters exchanged, and the average number of emotion and functional adjustment stickers and motivation graphic interface formats used [37].Research question 1c: is the Acceset text-based intervention (ie, the platform) feasible and acceptable (ie, safe and timely) as an ongoing mechanism of support that identifies individuals who are at an unacceptably high risk of mental health conditions?Hypothesis 1c: digital peer support is feasible and acceptable in offering support for emerging adults’ mental well-being by identifying individuals who are at an unacceptably high risk of mental health conditions related to depression and suicidality, which is measured before and during engagement based on 3 means—specifically, the Acceset algorithm detection of the content of the letters, the moderators’ vetting of the content of seekers’ letters, and the seekers’ self-report responses to the 9-item Patient Health Questionnaire [38] (refer to the Implementation Outcomes section for details [37]).Aim 2: the second aim is to elucidate whether Acceset digital peer support harnesses the 4 components of emerging adult mental health—mattering, selfhood, compassion, and mindfulness.Research question 2a: does Acceset digital peer support enhance the 4 components among seekers and befrienders?Hypothesis 2a: Acceset digital peer support (training) increases the 4 components among befrienders (before and after training) and seekers (over the course of the study across 4 time points).Research question 2b: is Acceset digital peer support effective in improving emerging adult mental well-being?Hypothesis 2b: digital peer support leads to significantly better mental well-being of seekers compared with the control group. This effect is sustained beyond the period of the intervention.Aim 3: the third aim is to investigate the mechanism of change in emerging adult mental well-being involving digital peer support (delivered by the Acceset platform).Research question 3: what is the mechanism explaining the change in emerging adult mental well-being involving digital peer support?Hypothesis 3: the initial level and rate of change (ie, growth factors) of befrienders’ web-based support positively predict the growth factors of seekers’ psychological well-being in accordance with latent growth curve modeling.

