The moderation protocol at the participant recruitment stage entails the screening of seekers using a validated psychological scale—the 9-item Patient Health Questionnaire (PHQ-9)—to exclude individuals at high risk of depression and suicidality. During the intervention phase, befrienders are also trained to alert moderators when seekers are at an unacceptably high risk of depression and suicidality, and the moderator vets all the letter exchanges between the seekers and befrienders for content of high negativity and suicidal thoughts and expressions. This moderation protocol aims to identify seekers who are at an unacceptably high risk of depression and suicidality and refer them to an appropriate mental health care provider, including counseling centers and hotlines, on the NUS campus.

Each befriender will provide support to 3 seekers, receive notification from the Acceset platform on incoming letters, and work in partnership with the moderators to address the seekers’ issues during the 3 weeks of letter exchange. Befrienders have the choice to discontinue the letter exchange with seekers if they feel discomfort having to address issues that they find challenging by informing trained moderators. Given the sensitive nature of the letter content, there may be issues that befrienders will be exposed to that they are not fully comfortable with and may cause distress. Therefore, it is a deliberate design to ensure that the befrienders are not left on their own in handling cases and that they work in partnership with the 2 trained and certified moderators to address the seekers’ issues. The first point of contact for the befriender will be the 2 trained and certified moderators. In such cases, the befriender’s workload decreases to 2 seekers.

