The system will inform the seeker and obtain their consent to continue the conversation with a new befriender or end the letter thread. If the seeker chooses to continue, the system will notify all befrienders of the availability of an ongoing case, and interested befrienders can take it up. In addition, other trained befrienders (whom Acceset has trained beyond the recruited 30 befrienders for this study) will be activated to take up the case if no existing befrienders take it up. Similarly, when befrienders drop out of the study during the 3 weeks of letter exchanges, they will be replaced with other trained befrienders. Befrienders’, seekers’, and moderators’ use of the Acceset platform is to remain completely anonymous such that the 3 parties do not have direct contact with one another, and seekers do not have discretion to switch befrienders on their own. In the event of disagreement between seekers and befrienders (eg, seekers are concerned with how their issues are not adequately addressed during the letter exchange), they will be able to notify the study team. The system will inform the seeker and obtain their consent to continue the conversation with a new befriender or end the letter thread. If the seeker chooses to continue, the system will notify all befrienders of the availability of an ongoing case, and interested befrienders can take it up. However, it should be noted that such situations will be rare given that moderators will vet all letter exchanges and work in partnership with befrienders to ensure that their responses are satisfactory. If seekers drop out of the study, their befrienders will continue with the reduced workload.

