### Digital Peer Support Training

The core objective of Acceset is to enable peer befrienders to effectively support peer seekers. Befrienders will receive 4 hours of web-based training conducted by a licensed clinical or educational psychologist. This training consists of 1 hour of instructional content that enhances the befriender’s knowledge of mattering, selfhood, compassion, and mindfulness and 2 hours of workshop training on the practical skills of applying these components to provide effective peer support.

Selfhood refers to self-knowledge (an awareness of one’s strengths and unique qualities) [41]. The second type of selfhood is the interpersonal self (how the self evolves based on our interactions and relationships with others). The interpersonal self creates and sustains relationships and fulfills important roles to keep a favored position in the social system. The third type of selfhood refers to the self as an agent (having agency, control, and persistence in achieving a goal despite failure, frustration, and discouragement). Mattering, which refers to the extent to which we are important to the world and people around us [42], consists of three components: (1) importance (the interest and concern others bestow on us), (2) attention (from others; the extent to which people are aware of our presence and unique qualities), and (3) reliance (the degree to which others turn to us and make us feel that we are needed).

Compassion comprises 3 theoretical orientations—having compassion for others, receiving compassion from others, and having self-compassion—in reducing psychological distress and symptomologies [43], and there are 3 stages of developing compassion based on the well-established Compassion Cultivation Training with evidence from accumulating RCTs [44]. In the first stage, individuals become aware of their distress and develop self-compassion; in the second stage, they develop affective concern; and, in the third stage, they gain personal insights into the wish and readiness to relieve one’s distress [44]. Mindfulness will be regarded as a flexible cognitive state in which individuals are actively present and notice novel aspects in both the environment and one’s perspectives [45].

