The proficiency of befrienders in applying these digital support skills will be evaluated through simulation and homework activities in which they will apply these skills to simulated letters that are adapted from actual cases of peer seeker emotional disclosure on the Acceset platform. All assignments will be reviewed and given feedback on. At the end of the training, befrienders are expected to apply the 4 components to their assigned peers’ disclosed emotional experiences. All participants who complete the training will receive a training certificate and will be invited to take on live cases and be part of the study.

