The seeker-befriender interaction dynamic is facilitated digitally, with no in-person visits or interactions. Before and during the letter-writing process, a pop-up message reminds both befrienders and seekers that the use of the Acceset platform is to remain completely anonymous and that personal information may not be revealed in any way. In matching befrienders and seekers, 3 factors are considered: the timing when seekers reach out, the availability of befrienders, and befrienders’ knowledge of the nature of the seekers’ emotional experiences. Some befrienders may have more in-depth knowledge of certain issues based on their lived experiences and will prefer to support seekers on those issues. Thus, when the seekers write a letter, the social context of the letter is made known to the befriender, who will then select their preferred seeker based on their ability to relate and respond. The approach of matching befrienders and seekers is intended to facilitate effective peer support intervention [29]. Through the digital peer support training and the guidance of the moderators—certified counselors who will vet the e-letter drafts from the befrienders—the befriender’s role is to provide support by enhancing a sense of mattering, strengthening selfhood, exploring compassion, and cultivating mindfulness among seekers. Importantly, it is not the responsibility of the befriender to serve as an advisor, solve the seekers’ problems, or provide diagnoses of potential mental health issues.

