#### Implementation Outcomes

For research question 1a and hypothesis 1a, we will determine whether Acceset digital peer support training is an effective curriculum for befrienders in providing effective peer support. We will assess the adoption of and fidelity to the training curriculum through the letter exchanges between seekers and befrienders. The text of the letter exchanges will be evaluated in terms of the extent to which befrienders display fidelity in applying the 4 components of psychological well-being in response to seekers’ disclosure. All correspondence will be anonymized before analysis, and the seekers’ letters will only be used to provide content for the befrienders’ responses. With respect to research question 1b, hypothesis 1b, research question 1c, and hypothesis 1c, we will evaluate the feasibility and acceptability of sustaining access to web-based peer support in terms of (1) initial and sustained engagement of seekers, befrienders, and moderators (ie, certified counselors); (2) the use of technical features of the Acceset platform; and (3) the identification of participants with high risk of mental health conditions relating to depression and suicidality.

This study will assess the waiting period for a seeker to receive a response. Delays (defined as a >48-hour waiting period) will be categorized based on the following reasons: (1) technical factors (eg, the befriender is not able to log into the platform to respond in time) and (2) human factors (eg, the befriender drops out from the study, and no replacement is found in time). An acceptable response time is within 48 hours, and this is emphasized during Acceset digital peer support training for befrienders. The seeker dropout rate at each stage of engagement with the Acceset platform will be assessed based on (1) the number of visits to the study registration website, (2) the number of participants who registered with Acceset, (3) the average number of letters exchanged, and (4) the average number of emotion and functional adjustment stickers and motivation GIFs used.

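### Hypothesis 1a scores training fidelity on letters that moderators have already vetted, so the result cannot be credited to training alone

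*Protocol article*

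**What the plan says.** The hypothesis (Protocol article, Aims and hypotheses, Hypothesis 1a) is that "the digital peer support training is effective for befrienders in providing peer support, as demonstrated by the adoption of and fidelity to the training curriculum". The Implementation Outcomes section names the source of evidence: "We will assess the adoption of and fidelity to the training curriculum through the letter exchanges between seekers and befrienders". It then says what is scored: "The text of the letter exchanges will be evaluated in terms of the extent to which befrienders display fidelity in applying the 4 components".

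Three passages describe what moderators do to the same letters:

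- Peer Emotional Disclosure describes moderators as "certified counselors who will vet the e-letter drafts from the befrienders". The same sentence gives training and moderator guidance together as the means by which the befriender delivers the 4 components.
- Participants and Study Setting, on disagreements between seekers and befrienders, says that "moderators will vet all letter exchanges and work in partnership with befrienders to ensure that their responses are satisfactory".
- Participants and Study Setting, on the moderation protocol, gives a safety purpose: "the moderator vets all the letter exchanges between the seekers and befrienders for content of high negativity and suicidal thoughts and expressions".

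On who writes live letters, Digital Peer Support Training says "All participants who complete the training will receive a training certificate and will be invited to take on live cases". That section also plans a proficiency check on simulated letters and homework. On the length of the training it says "Befrienders will receive 4 hours of web-based training", then itemises 1 hour of content and 2 hours of workshop. The Strengths section gives 3 hours.

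**The concern.** Research question 1a asks whether the training curriculum works. The text chosen to answer it is the joint product of a trained befriender and a certified counselor. If the sent letters show the 4 components well, the plan as written credits the curriculum, although some of that quality may come from the moderator. The documents do not say that the unvetted draft is scored or that moderator changes are recorded, so the two contributions could not be separated afterwards.

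A smaller, related point concerns adoption. The invitation to live cases goes to those who complete training. Adoption read from letters therefore has no place for people who started training and left.

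What is at stake is the wording of the Hypothesis 1a conclusion: whether the trial can say that the training produced the skill, or only that training with moderation produced acceptable letters.

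**Working it through.** **No figure to reproduce.** The article gives no fidelity score, threshold, training-completion rate or moderator-edit rate for Hypothesis 1a. The only power statement (significance level .05, 80% power) is not tied to this outcome.

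**Setting the passages side by side.**

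1. Target of the conclusion: the training curriculum (Hypothesis 1a).
2. Material scored: the text of exchanged letters (Implementation Outcomes).
3. State of that material: vetted as drafts by counselors (Peer Emotional Disclosure), with moderators working with befrienders on how satisfactory the replies are (Participants and Study Setting).
4. Overlap between moderator input and what is scored: Peer Emotional Disclosure lists moderator guidance as a route to the same 4 components.

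Steps 3 and 4 place a second influence between the training and the scored text.

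**How large could it be? Illustration only; every input is assumed.** Let f be the share of unaided drafts that show the components, and m the share of deficient drafts that moderators improve on those components.

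- Scored fidelity = f + (1 − f)m
- Excess over unaided fidelity = (1 − f)m

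| f | m = 0 | m = 0.25 | m = 0.50 |
|---|---|---|---|
| 0.5 | 0.50 (excess 0) | 0.625 (12.5 points) | 0.75 (25 points) |
| 0.6 | 0.60 (0) | 0.70 (10) | 0.80 (20) |
| 0.7 | 0.70 (0) | 0.775 (7.5) | 0.85 (15) |
| 0.8 | 0.80 (0) | 0.85 (5) | 0.90 (10) |

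For example, with f = 0.6 and m = 0.25: 0.6 + 0.4 × 0.25 = 0.70, an excess of 10 points. The column m = 0 is the case where vetting touches only safety content.

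**Adoption denominator.** Let c be the share of starters who complete training (not stated; assumed 0.7 to 1). If every completer adopted the curriculum, adoption would read 100% among letter writers and c among starters, that is 70% to 100%.

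**Training duration.** 1 hour + 2 hours = 3 hours. This agrees with the Strengths section but not with the 4 hours stated just before the itemisation.

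**The case against.** The best defence is that vetting may be a safety screen and nothing more. The moderation protocol and the Implementation Outcomes section both describe it in terms of negativity and suicidal content. The remark about satisfactory replies comes in a paragraph on why disputes should be rare, and no passage says that moderators rewrite letters or add the 4 components. This stands against any claim that fidelity is certainly inflated. It does not restore attribution to training, because Peer Emotional Disclosure itself gives moderator guidance a part in delivering the components.

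Second, letters are not the only evidence. Proficiency is checked on simulated letters and homework, and the Principal Findings section ties the hypothesis to higher component scores after training than before. Neither is described as passing through moderator vetting of live letters. This stands in part. However, the simulated work is not listed as an outcome for Hypothesis 1a in the Implementation Outcomes section, and the before/after scores concern befrienders' own attributes rather than their skill in supporting a peer.

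Third, the intervention as described includes moderators, so sent letters are a fair measure of the package as delivered. That is right. The difficulty is only that research question 1a asks about the training.

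Fourth, fidelity can be observed only in people who write letters. That also stands, so the completion point is confined to adoption.

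**Conclusion.** The concern holds in a limited form. Fidelity scored on sent letters reflects training plus moderator input and cannot be attributed to training alone. If there is a distortion, its likely direction is upward, because moderators act to improve replies. Its size is unknown: 0 to 25 points over the assumed range (f from 0.5 to 0.8, m from 0 to 0.5), and nil if moderators leave component content untouched.

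A reader might infer more, and the documents do not support it:

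- *That the measure is known to overstate the training effect, perhaps heavily.* A large figure needs a high moderator-repair rate, and the article gives none.
- *That restricting to completers biases fidelity.* It bears on adoption, and no completion rate is given.
- *That the scalability case depends on this result.* The Strengths section rests scalability mainly on the web format and the fit with existing curricula, and its remark on affordability includes professional moderators.

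The conflict over training hours is real, but it is a separate matter and adds nothing to the vetting point.

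**What to change.** 1. Where drafts were kept, score each befriender's draft as submitted, before any moderator comment, and report the sent version alongside. The difference shows the moderators' contribution.
2. Where drafts were not kept, report the simulated-letter proficiency as a Hypothesis 1a measure and label the letter result *training plus moderation* instead of an effect of training.
3. Report adoption with everyone who started training as the denominator.
4. Separately, reconcile the training durations in Digital Peer Support Training (4 hours against 1 plus 2 hours) and in the Strengths section (3 hours).

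**Cost.** Item 1 means extra coding of saved drafts. It is possible only if they exist: the Results section says data collection finished in June 2022, so a change to what the platform stores would recover nothing for this trial. The data management section mentions storing letter exchange content and does not mention drafts. Item 2 costs a more modest conclusion. Item 3 needs a count of training starters. Item 4 is an edit to the text. Data analysis is described as still in progress, so the reporting changes can still be made.

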### Eligibility Criteria

The seeker inclusion criteria are as follows: emerging adults aged 19 to 25 years who are distressed but healthy—specifically, these individuals should exhibit some symptoms but have not been formally diagnosed with depression, anxiety, or a mental health disorder. The exclusion criteria (seekers) will include emerging adults who, during screening, are deemed to be at a high risk of suicide using a validated and standardized psychological scale (PHQ-9) [37,38]. On the basis of empirical studies, the proposed cutoff is PHQ-9 >9, which has a sensitivity of 88% and specificity of 88% for major depression [37]. Above a score of 9, seekers will not be recruited for the study, and they will be referred or directed to different clinical mental health support providers, including counseling centers and hotlines, on the NUS campus.

The rationale for including individuals who do not meet the criteria for depression is that the Acceset intervention focuses on befrienders as peer supporters to seekers, and these befrienders are not certified and accredited counselors, unlike moderators. Importantly, it is not the responsibility of the befriender to serve as an advisor, solve the seekers’ problems, or provide diagnoses of potential mental health issues. Inclusion of individuals who meet the criteria for depression would require support from professional counselors who have formal trainings and certifications. However, Acceset as an intervention platform is designed primarily for a healthy population of young people without formal diagnoses of mental health conditions to provide peer support.

The inclusion eligibility criteria also apply to befrienders, with an additional criterion of being aged ≥21 years. Seeker exclusion criteria apply to both befrienders and moderators. Moderator inclusion criteria are as follows: adults aged ≥21 years with certified trainings and accreditations (ie, at least a master’s degree in social sciences or Counseling that is recognized by the Ministry of Education, Singapore, and the Executive Counselling and Training Academy) and professional experiences in providing counseling services to emerging adults. The exclusion criteria apply to both seekers and befrienders.

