With regard to user referral to appropriate mental health support providers, the seeker-befriender-moderator interaction will identify participants at an unacceptably high risk of depression and suicidality before and during engagement based on 3 means. First, the Acceset algorithm will scan the content of the letter exchanges for high negativity and suicidal thoughts and expressions. Second, moderators with the required background and assessment tools will identify seekers at risk by vetting all the letter exchanges for high negativity and suicidal thoughts and expressions. Third, seekers will self-report their responses to the PHQ-9, and those that meet the clinical cutoff scores (PHQ-9 >9) will be excluded at the start of the study. During the course of the study across the 4 time points, seekers with an unacceptably high risk of depression and suicidality (PHQ-9 >9) will be referred to an appropriate mental health care provider, including counseling centers and hotlines, on the NUS campus. Seekers’ self-reported responses to the PHQ-9 serve as the primary risk assessment to make referrals to appropriate mental health support providers.

At recruitment, we will assess the percentage of participants identified as being at an unacceptably high risk of depression and suicidality meeting the clinical cutoff of PHQ-9 >9 that has a sensitivity of 88% and specificity of 88% for major depression [38] and exclude them from the study. During the course of the study, we will ascertain the percentage of events when a befriender correctly alerts the moderator that the seeker is at an unacceptably high risk of depression and suicidality as confirmed by the moderator, who will vet every letter exchange. During the course of the study and for every letter exchange, we will tabulate the percentage of events when a moderator correctly identifies a seeker with an unacceptably high risk of depression and suicidality. Both the befrienders and moderators will use the PHQ-9 as a systematized coding structure to code seekers’ letter content to ensure generalizability and validity in risk assessment across both coders—befrienders and moderators. Finally, we will tabulate the percentage of events when a seeker who is at an unacceptably high risk of depression and suicidality (both during the recruitment process and during engagement with the platform) receives directions to an appropriate mental health care provider, including counseling centers and hotlines, on the NUS campus.

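### The letter-based risk-detection percentages for hypothesis 1c have no independent reference, so a seeker whom the moderator misses is not counted as a miss

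*Protocol article*

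**What the plan says.** Textbox 1 (Aims and hypotheses) puts hypothesis 1c in terms of identifying people at high risk, "which is measured before and during engagement based on 3 means": the algorithm's scan of the letters, the moderators' vetting of the letters, and the seekers' self-reported PHQ-9.

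Implementation Outcomes then sets out what will be tabulated during the study:

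- **Befrienders:** "the percentage of events when a befriender correctly alerts the moderator that the seeker is at an unacceptably high risk of depression and suicidality", with correctness settled "as confirmed by the moderator, who will vet every letter exchange".
- **Moderators:** "we will tabulate the percentage of events when a moderator correctly identifies a seeker with an unacceptably high risk of depression and suicidality". No reference is named.
- **Algorithm:** its scan is described, but no measure of its performance is given.
- **Referral:** the percentage of at-risk events in which the seeker is directed to care.

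The same section says that befrienders and moderators "will use the PHQ-9 as a systematized coding structure to code" the letters, and gives validity across the two coders as part of the reason. It also states: "Seekers’ self-reported responses to the PHQ-9 serve as the primary risk assessment to make referrals to appropriate mental health support providers". That questionnaire is applied across the 4 time points, with referral above 9. On the cutoff itself, Eligibility Criteria says "the proposed cutoff is PHQ-9 >9, which has a sensitivity of 88% and specificity of 88% for major depression".

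**The concern.** A percentage of correct identifications means something only if correctness is decided by something other than the rater being assessed, and if the denominator includes the cases that the rater failed to find. The text gives the befriender percentage a reference that reads the same letters. It gives the moderator percentage no reference at all. Neither percentage has a stated denominator.

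Two raters coding the same letters with the same frame can show how far they agree, which is reliability. They cannot show that either has found the seekers who are truly at risk, which is validity. The article treats the common frame as a safeguard of validity.

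At stake is the conclusion about screening by letter. Hypothesis 1c presents identification of at-risk seekers as evidence that the platform is feasible and acceptable, in the sense of safe and timely. A measure that does not fall when the moderator overlooks someone cannot support that for the letter-based routes.

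**Working it through.** The article states no target, sample size or expected rate for hypothesis 1c, so there is no figure to reproduce. The check is a comparison of the stated measures, followed by illustrative arithmetic.

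**1. What each measure is judged against**

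| Route | Stated reference | Compared with self-reported PHQ-9? |
|---|---|---|
| Befriender alert | Moderator | No |
| Moderator identification | None stated | No |
| Algorithm | No measure given | No |

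Take a seeker at risk whom the moderator does not flag. In the moderator percentage, nothing named in the text would reveal the omission. In the befriender percentage there are two cases. If the befriender also stayed silent, there is no discrepancy to record. If the befriender did alert, the alert is unconfirmed and does not count as correct. In neither case is a miss by the moderator recorded.

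**2. Share of correct flags against sensitivity**

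From the article: 50 seekers in arm 1. Assumed: 10 have PHQ-9 >9 at week 3, and the moderators flag 5 of these and nobody else.

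- Share of flags that are correct = TP/(TP+FP) = 5/(5+0) = 100%
- Sensitivity = TP/(TP+FN) = 5/(5+5) = 50%
- Seekers missed = 5

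Over a wider assumed range (10% to 40% of the 50 at risk, moderator sensitivity 50% to 90%), the expected number missed runs from 50 × 0.10 × (1 − 0.90) = 0.5 to 50 × 0.40 × (1 − 0.50) = 10. If the moderator's own judgement also defined correctness, the moderator percentage would be 100% throughout.

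**3. The befriender percentage depends on a denominator that is not given**

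Assumed: 10 of 50 at risk, befriender sensitivity 70%, moderator sensitivity 90%, both specificities 90%, errors independent.

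- Flagged by both = 10 × 0.7 × 0.9 + 40 × 0.1 × 0.1 = 6.7
- Alerts raised = 10 × 0.7 + 40 × 0.1 = 11; confirmed share = 6.7/11 = 61%
- Moderator-positive = 10 × 0.9 + 40 × 0.1 = 13; alerted share = 6.7/13 = 52%
- Missed by the moderator = 10 × 0.1 = 1.0, of whom 0.7 were alerted by the befriender (scored as unconfirmed) and 0.3 by nobody

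The same data give 61% or 52%, and neither figure contains the one seeker whom the moderator missed.

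**4. Precision that a proper comparison could reach**

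Exact (Clopper-Pearson) lower 95% limit when all n cases are detected = 0.025^(1/n):

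- n = 5: 0.478
- n = 10: 0.692

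With some misses, the exact 95% intervals are 28% to 99% for 4/5, 44% to 97% for 8/10, and 56% to 94% for 16/20. The case numbers are assumptions.

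**The case against.** The strongest reply is that hypothesis 1c does not rest on these two percentages. Self-report is one of its three means, is the primary risk assessment, and leads to referral at the scheduled time points. In the example above, all 10 seekers would be identified by their week-3 questionnaire. The article also tabulates how often at-risk seekers are directed to care. This stands. A reader might infer that seekers missed in the letters go unnoticed, and the documents do not support that. It does not rescue the letter-based percentages, because a case found by questionnaire is no evidence that the algorithm, befriender or moderator found it.

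Three further strong readings are also unsupported:

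- **The moderator is their own reference, so the result confirms itself.** The article is silent on the moderator's reference. Self-confirmation is an inference from that silence.
- **The befriender figure is a positive predictive value.** No denominator is stated. Since moderators read every letter, befriender misses could be counted among moderator-positive events.
- **The shared frame builds in agreement.** Trained peers and certified counselors can code the same letter differently; the assumed example gives 61% or 52%.

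It can also be said that a condensed article may leave references and denominators to a fuller document. That is fair for the denominators alone. The point rests on what the section does fix: the moderator as reference for befrienders, a common coding frame offered as validity, and a separate risk measure assigned to referral and not to checking the letter flags.

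Finally, week-3 PHQ-9 is an imperfect reference. Participants and Study Setting says that seekers whose letters raise concern are linked to counseling at once, and Data Collection, Management, and Analyses expects some high-risk seekers to drop out. A sound early flag may therefore be followed by a low or missing week-3 score. This stands and shapes the fix.

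**Conclusion.** The concern holds in a limited form. As written, the letter-based part of hypothesis 1c is measured by percentages with no independent reference, the algorithm is not measured at all, and a seeker missed by the moderator is a miss in neither percentage. The trial could report that every flag was right while sensitivity was 50%, as in the assumed example. The defect limits what can be concluded about detection through letters. It does not show that missed seekers remain unidentified, since self-report can still find them at the next questionnaire.

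The size rests on assumptions that the article neither gives nor rules out: the number of seekers who pass the cutoff and the sensitivity of each route. The structural point does not depend on them. The accuracy quoted for the cutoff concerns major depression, so results against it describe depression risk and not suicidality. The change should be made, since it concerns a safety-related claim and uses data already planned.

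**What to change.** In arm 1, with one row per seeker, cross-tabulate each letter-based route (algorithm, befriender alert, moderator flag during the 3-week exchange) against self-reported PHQ-9 >9 at week 3.

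1. Report first the number and share of seekers with PHQ-9 >9 whom each route failed to flag, and whom no route flagged.
2. Then give sensitivity, specificity and positive predictive value with exact 95% intervals.
3. Show flagged seekers with a missing week-3 PHQ-9 separately. Do not read a flag followed by a low week-3 score as a clear false positive, because referral or dropout after the flag can change or remove that score.
4. Report befriender-moderator agreement on its own, labelled as reliability.
5. Describe the result as depression risk. Eligibility Criteria uses one cutoff for high risk of suicide while quoting accuracy for major depression; the sponsor must reconcile that wording.

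The cost is one extra table from data already collected. The drawbacks are few cases, wide intervals (lower limits of 48% for 5/5 and 69% for 10/10, with case numbers assumed), possibly a less favourable headline figure, and a single visit that only approximates risk over three weeks.
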